***Study visits***

*Screening visit*

When a patient meets ALL inclusion criteria and NONE of the exclusion criteria, he/she can be enrolled in the study. The criteria are judged based on data available from the patient’s file. Female patients of reproductive age should be screened with a urinary pregnancy test. QT prolongation or prior arrhythmia is not considered as an exclusion criterion for the study, ^9,11^ but may be considered in the decision making of the principal investigator. The same patient cannot be enrolled twice in this study.

*Patient follow-up*

Follow-up of every patient will be done daily until day 28 or hospital discharge (whatever comes first).

Visit 1 is on day 1. Procedures of this day include:

- Recording of demographics, medical history, co-morbidities (Charlson Comorbidity Index), ^17^ SOFA score (see APPENDIX II); Acute Physiology and Chronic Health Evaluation (APACHE) II score (see APPENDIX III), available blood cell count, biochemistry, coagulation time, urine output, blood gas analysis, recording of suspected infection site, available radiological findings, relevant for the current infection microbiology and antimicrobial susceptibility testing if available, administered antimicrobials, other administered drugs and need for source infection control either by percutaneous interventions or by any operation.
- Sampling of 35 ml of venous blood; 3ml is collected into one PAXgene tube or a tube with RNA*later*®; 9ml is collected into one pyrogen-free tube; and 24ml is collected into EDTA-coated tubes
- Collection of stool culture or rectal swab
- Administration of the study drug
- Evaluation of potential adverse events

Visit 2 is on day 2. Procedures of this day include:

- Recording of SOFA score (see APPENDIX II); available blood cell count, biochemistry, coagulation times, urine output, blood gas analysis, available radiological findings, relevant for the current infection microbiology and antimicrobial susceptibility testing if available, administered antimicrobials, other administered drugs and need for source infection control either by percutaneous interventions or by any operation.
- Survival status
- Administration of the study drug
- Evaluation of potential adverse events

Visit 3 is on day 3. Procedures of this day include:

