**Study Design**

The INCLASS study is a multicenter, international, placebo-controlled, double-blind, parallel group Randomized Clinical Trial (RCT). It is hypothesized that intravenous clarithromycin, as adjunctive treatment to standard of care for sepsis reduces all-cause 28-day mortality compared to placebo. The study aims to include 110 patients from 13 investigational sites, ICU and non-ICU, in Greece and in Belgium.

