**General principles**

- This analysis plan and the primary manuscript will include clinical data up to 90 days, transcriptomic and cell population (by flow cytometry) analyses; the entire cost-effectiveness analysis, cytokine analysis (including serum cytokine concentrations and cytokine production from supernatants of ex-vivo stimulated peripheral blood mononuclear cells-PBMCs) and microbiome analysis will be reported separately.
- Regarding flow cytometry analysis (including cell population and HLA-DR analysis), only samples from patients enrolled in sites proximal to the central lab (Athens) could be included in the current study.
- Regarding trasncriptomic analysis, only a subset of sample sequencing could be covered by the study funding at the time of the present statistical analysis plan. Thus, it was decided to only include in the primary manuscript samples from the subgroup of patients of extremely high severity (within the highest quartile of baseline SOFA score), to demonstrate differences between death and survival. The entire transcriptomic analysis, combined with metabolome, cytokine and microbiome analysis will be reported separately.
- All p-values will be two-sided and the level of significance will be <0.05.
- No interim analysis is planned.
- Regarding clinical data, cell populations and HLA-DR measurements, no adjustment for multiple comparisons is planned and all secondary outcomes will be viewed as exploratory. For transcriptomic data, statistically significant differences will be defined by Benjamini & Hochberg adjusted probabilities < 0.05 and absolute fold expression ≤−1.5 or ≥1.5.
- Analyses will be conducted primarily by the SPSS statistical software, version 24 (IBM) or later; transcriptomic data twill be analysed in the R statistical framework (Version 3.51, R Core Team 2014. R: A language and environment for statistical computing. R Foundation for Statistical Computing, Vienna, Austria)
- Results will be presented by order of importance, starting with the primary outcome first. Due to the nature of the study, additional exploratory analyses will be performed based on the primary and secondary outcomes, in an effort to identify potential host immune pathways modulated by the study drug.

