**Analyses for secondary outcomes**

The effect of the study arm on secondary outcomes will be compared with the Pearson chi-square test, or the two-sided Fisher’s exact test for 90-day mortality, early sepsis response and sepsis resolution, as well as new sepsis incidence. Clinical secondary outcomes will be evaluated on an ITT basis.

- Regarding 90-day mortality, the following subgroup analyses are planned (for all subpopulations identified): per country; per ward of enrollment (ICU or general ward); per protocol (according to whether the study intervention was complete -all 4 doses received); per presence of septic shock (already present in the protocol); per highest SOFA score (defined as higher or lower than the upper SOFA quartile of the population); per presence of ARDS; per initial infectious site; per adequacy of empirical antimicrobial treatment; and per Gram-negative vs non-Gram negative pathogen, among infections with identified pathogens. Interactions between subgroups and arm of treatment were assessed with Breslow-Day test and confirmed with logistic regression for the primary outcome.
- The time to new sepsis incidence will be compared only for patients experiencing a new sepsis episode both by the Mann-Whitney test, and as Cox-regression analysis of the treatment effect on the time to new sepsis episode, with death as competing event.
- Cell populations and monocytic HLA-DR variables will be assessed using Student’s t-test (for variables following a normal distribution), Mann-Whitney U (for variables following a skewed distribution), as appropriate. Overtime changes will be assessed by the k-related samples non-parametric Friedman test, separately per study arm, and the mixed ANOVA test with time and study arm as within-subject and between-subject factors respectively.
- Transcriptomic data wil be illustrated by Volcano plots for differential expression of genes among study groups, while gene set enrichement analysis will also be performed to identify pathways of transcriptomic changes among study groups. Any need for additional (post-hoc) analyses will be re-evaluated. Functionality of differentially expressed transcripts will be assessed by the ENCODE project.

Raw sequence data and count data will be uploaded on National Center for Biotechnology Information (NCBI) gene expression omnibus (GEO), to be publicly available.

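### The between-arm tests of cell populations and HLA-DR never use the day-1 value as a covariate, a precision gain forgone at no cost in a small exploratory subset

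*Supplement*

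**What the plan says.** SAP, Analyses for secondary outcomes: "Cell populations and monocytic HLA-DR variables will be assessed using" a t-test where the distribution is normal, with Mann-Whitney U being the alternative for skewed variables. Changes over time are assessed by a Friedman test run separately in each arm and by "the mixed ANOVA test with time and study arm as within-subject and between-subject factors respectively". No covariate is named, no visit is named for the two-sample tests, and no term of the ANOVA is singled out as the treatment comparison.

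Protocol version 2, Study visits, draws the blood on days 1, 5 and 10; at each of these visits "24ml is collected into EDTA-coated tubes". Laboratory analysis assigns part of that blood to flow cytometry. Under Visit 1, blood sampling is listed above study drug administration, but no sentence fixes that order.

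SAP, General principles, restricts flow cytometry: "only samples from patients enrolled in sites proximal to the central lab (Athens) could be included in the current study". It gives no number of patients. The same section sets the test level ("All p-values will be two-sided and the level of significance will be <0.05") and the status of these outcomes: "no adjustment for multiple comparisons is planned and all secondary outcomes will be viewed as exploratory".

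**The concern.** A marker measured before and after treatment is usually compared between randomised arms with the baseline value as a covariate. This removes the part of the follow-up variance that baseline predicts and corrects for chance differences at the start. The SAP does name adjustment variables for 28-day mortality, but none for these markers.

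The four planned tests do not fill the gap. The t-test and Mann-Whitney test at a follow-up visit leave day 1 out. The Friedman test compares nothing between arms. In the mixed ANOVA, the time-by-arm term is a change-from-baseline contrast if day 1 is a level, while the arm main effect averages in the day-1 value and so dilutes any treatment effect. A reader cannot tell which of the two will be reported as the effect of clarithromycin.

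At stake is the chance of detecting a real effect on immune markers in a subset that only some sites can supply. The SAP also states insight into mechanism as an aim of the study.

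**Working it through.** **The plan's own figure.** The only size calculation is for mortality: 55% versus 30%, alpha 0.10, power 0.8. A two-sided, continuity-corrected calculation returns 55 per arm, as stated. It does not bear on these markers, for which no size, SD, correlation or power is given.

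**Subset size (assumed).** "The study aims to include 110 patients from 13 investigational sites, ICU and non-ICU, in Greece and in Belgium". The site list shows 5 of the 13 in Athens. With equal recruitment, 110 × 5/13 = 42.3, or about 21 per arm at 1:1. Deaths and missing samples by days 5 and 10 would lower this, so 15 per arm was also tried.

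**Variance factors.** With equal variances at each visit and correlation ρ between baseline and follow-up:

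- value at one follow-up visit, unadjusted: 1
- change score (the interaction with two visits): 2(1 − ρ)
- ANCOVA with day 1 as covariate: 1 − ρ²

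ANCOVA is never worse: 1 − (1 − ρ²) = ρ² ≥ 0 and 2(1 − ρ) − (1 − ρ²) = (1 − ρ)² ≥ 0.

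| ρ | unadjusted | change score | ANCOVA |
|---|---|---|---|
| 0.3 | 1 | 1.40 | 0.91 |
| 0.5 | 1 | 1.00 | 0.75 |
| 0.7 | 1 | 0.60 | 0.51 |

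**Power.** Noncentral t, two-sided 0.05, noncentrality (d/√V) × √(n/2), where V is the variance factor and d the standardised effect; 2n − 2 degrees of freedom, one fewer for ANCOVA. Example: n = 21 and d = 0.8 give 0.8 × √10.5 = 2.59 unadjusted; at ρ = 0.5, ANCOVA gives 2.59/√0.75 = 2.99. Power goes from 71.6% to 83.1%.

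At 21 per arm and ρ = 0.5 (where the change score has the same power as the unadjusted test):

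| d | unadjusted | ANCOVA | gain (points) |
|---|---|---|---|
| 0.6 | 47.5% | 59.1% | 11.6 |
| 0.7 | 60.0% | 72.4% | 12.4 |
| 0.8 | 71.6% | 83.1% | 11.6 |
| 0.87 | 78.5% | 88.8% | 10.2 |

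**Three visits.** Take equal correlation between visits and the same effect on days 5 and 10. The 2-df time-by-arm F test has noncentrality n·d²/[3(1 − ρ)]; for n = 21, d = 0.8, ρ = 0.5 this is 21 × 0.64/1.5 = 8.96. The arm main effect has effect 2d/3 and variance factor (1 + 2ρ)/3. At 21 per arm and d = 0.8:

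| ρ | unadjusted | change score | 3-visit interaction | arm main effect | single-visit ANCOVA |
|---|---|---|---|---|---|
| 0.3 | 71.6% | 57.1% | 59.6% | 63.7% | 75.5% |
| 0.5 | 71.6% | 71.6% | 75.2% | 54.2% | 83.1% |
| 0.7 | 71.6% | 90.4% | 93.5% | 47.0% | 94.3% |

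**Ranges.** For 21 per arm, ρ from 0.3 to 0.7 and d from 0.5 to 0.87:

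- over the unadjusted test, the gain is about 3 to 28 points
- over the two-visit change score, it is about 18 down to 3 points
- over the three-visit interaction at ρ = 0.5, it is 72.4 − 62.8 = 9.6 points at d = 0.7 and 88.8 − 82.4 = 6.4 at d = 0.87
- over the same test at ρ = 0.7 and the same two effects, it is 0 to 2 points

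At 15 per arm with ρ = 0.5 and d from 0.5 to 1.0, the gain over the unadjusted test is 7 to 12 points. The three-visit comparison sets one follow-up visit against two. When both average days 5 and 10 (21 per arm, d = 0.8, ρ = 0.5), the change score has 83.2% and ANCOVA 94.7%.

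**Chance imbalance.** With 21 per arm the baseline difference has standard error √(2/21) = 0.31 SD, so about one trial in three would differ by 0.3 SD or more at the start.

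**The case against.** The strongest reply is that the mixed ANOVA does use baseline. The SAP assigns it to change over time, and with day 1 as a level its interaction is a valid comparison of changes. What then separates it from ANCOVA is efficiency, and at ρ = 0.7 with three visits the difference is negligible. This stands. A reader might infer that the plan ignores baseline altogether; that is true of the two-sample tests, and not of the interaction.

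Three other strong readings also fail.

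- A reader might take 10 to 12 points in 42 patients as a property of the plan. The points need an assumed ρ of 0.5 and a suitable effect size, and the 42 needs equal recruitment; the documents give none of these.
- A reader might infer that unadjusted tests would bias the result. Under randomisation they keep their type I error; a chance imbalance adds noise to the estimate and is not a systematic error.
- A reader might take these markers as the only mechanistic comparison of the arms in the main paper. The SAP also plans differential expression and enrichment among study groups, although General principles limits those samples to the top SOFA quartile, to contrast death with survival.

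It is also fair to say that these outcomes are exploratory and no power is claimed for them. That lowers the priority, but gives no reason to leave a measured covariate unused.

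**Conclusion.** The point holds as a minor, inexpensive improvement. No planned test uses the day-1 value as a covariate, and the SAP does not identify the treatment contrast in the mixed ANOVA. Under equal variances, the residual variance with adjustment never exceeds that of the unadjusted test or the change score. The gain is large against the unadjusted test when ρ is high, large against the change score when ρ is low, and close to nil against the three-visit interaction at ρ = 0.7.

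All power figures rest on assumed values of ρ, d and subset size, on complete data, and on approximately normal outcomes; they do not describe the Mann-Whitney test. That day 1 is a pre-treatment value is inferred from the order of the Visit 1 list. The primary mortality analysis is untouched.

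**What to change.** In SAP, Analyses for secondary outcomes, make the between-arm analysis of each cell-population and HLA-DR variable an ANCOVA of the day-5 value, and of the day-10 value, on study arm with the day-1 value as covariate. Log-transform skewed variables. A mixed model with the post-baseline visits as outcomes and the day-1 value as covariate would serve equally. Name the treatment contrast and report the adjusted difference with its 95% CI. Keep the t-test, Mann-Whitney and Friedman results as descriptive.

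Add that the day-1 sample counts as baseline only if it was drawn before the first dose, and give the number of patients with a usable sample at each visit. Patients without a day-1 sample can be kept with a constrained-baseline model.

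The cost is one or two sentences of SAP text and one degree of freedom per model; no new samples or data are needed. The change does not deal with follow-up values that are missing because a patient has died.

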- Evaluation of resolution of the infection and potential recurrence of infection according to the judgment of the attending physician
- Evaluation of potential adverse events

Visit 10 is on day 10. Procedures of this day include:

- Recording of SOFA score (see APPENDIX II); available blood cell count, biochemistry, coagulation times, urine output, blood gases, available radiological findings, clinically relevant microbiology and antimicrobial susceptibility testing, administered antimicrobials, other administered drugs and need for source infection control either by percutaneous interventions or by any operation.
- Survival status
- Evaluation of resolution of the infection and potential recurrence of infection according to the attending physician
- Sampling of 33 ml of venous blood; 9ml is collected into one pyrogen-free tube; and 24ml is collected into EDTA-coated tubes
- Evaluation of potential adverse events

Visits 11-28 are on days 11-28 respectively. They include

- Recording of SOFA score if available
- Administered antimicrobials, other administered drugs and need for source infection control either by percutaneous interventions or by any operation.
- Survival status
- Evaluation of resolution of the infection and potential infection recurrence according to the judgment of the attending physician
- Evaluation of potential adverse events

If the patient is discharged before day 28, a phone call will be performed on day 28 to assess survival status, need for new hospitalization or antibiotic therapy and potential adverse events. End-of-life decisions, if any, will be recorded.

Last visit: A phone call follow-up will be done on day 90 to assess survival status. If available, data concerning any new hospitalization, or antibiotic cure and potential adverse events will be collected during that phone call. Moreover, a self or proxy-assessment of health-related quality of life will be performed through the EQ-5D-3L^™^ questionnaire on the same visit (see APPENDIX IV) ^18^.

All information will be recorded on a specific paper Case Report Form (CRF).

The procedure to follow at each study visit is shown in APPENDIX V.

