***Laboratory analysis***

Collected samples will be transported to the central lab that is the Laboratory of Immunology and Infectious Diseases of the 4^th^ Department of Internal Medicine, ATTIKON University General Hospital, Athens, Greece. Analysis will be done as follows:

- PAXgene tubes or tubes with RNA*later*® for will be stored in -80°C for full transcriptomics
- EDTA tubes will be used: partly for direct isolation of peripheral blood mononuclear cells and further cytokine stimulation, partly for flow cytometry, and partly for whole blood immune functional assay. The remaining blood in EDTA tubes will be centrifuged and plasma will be stored in -20°C for metabolomics, cytokine analysis with enzyme immunoassay (EIA) and antibiotic concentration measurement with high-performance liquid chromatography (HPLC) in patients receiving meropenem, tigecyclin or colistin; leucocyte buffy coat remaining after plasma aspiration with sterile pipette will be equally stored in -20°C for genome analysis.
- Serum isolated from pyrogen and anticoagulant-free tube after centrifugation will be stored in -20°C to be used for metobolomic analysis and serum markers.
- Stool or rectal swab will be stored in -80°C, to be later processed for 16S rRNA sequencing of the intestinal microbiome.

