| Resolution/ recurrence of infection** |  |  |  |  |  |  | x | x | x | x | x | x | x | x | x | x | x | x | x | x | x | x | x | x | x | x | x | x |  | |
| AE monitoring | x | x | x | x | x | x | x | x | x | x |  |  |  |  |  |  |  |  |  |  |  |  |  |  |  |  |  |  |  | |
| Microbiology** | x | x | x | x | x | x | x | x | x | x | x | x | x | x | x | x | x | x | x | x | x | x | x | x | x | x | x | x |  | |
| Pregnancy test*** | x |  |  |  |  |  |  |  |  |  |  |  |  |  |  |  |  |  |  |  |  |  |  |  |  |  |  |  |  | |
| PAX Gene | x |  |  |  | x |  |  |  |  |  |  |  |  |  |  |  |  |  |  |  |  |  |  |  |  |  |  |  |  | |
| Serum metabolomics | x |  |  |  | x |  |  |  |  | x |  |  |  |  |  |  |  |  |  |  |  |  |  |  |  |  |  |  |  | |
| PBMCs isolation | x |  |  |  | x |  |  |  |  | x |  |  |  |  |  |  |  |  |  |  |  |  |  |  |  |  |  |  |  | |
| Stool sample | x |  |  |  | x |  |  |  |  |  |  |  |  |  |  |  |  |  |  |  |  |  |  |  |  |  |  |  |  | |

- * SOFA score: if available according to usual clinical practice. On days where SOFA components are not available (e.g. no blood analysis programed by the physician or discharged patient), the last known value will be recorded.
- ** If available and justified by clinical context ***For female patients of reproductive age

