**Descriptives and baseline comparisons**

- Categorical variables will be expressed as counts (and percentages), providing the number of patients or events entered at every step of the analysis.
- The Kolmogorov-Smirnov test for normality will be conducted to the entire population and the arms of study intervention. Continuous variables with normal distribution will be presented with their mean and standard deviation (SD), those with a skewed distribution will be presented with their median and quartiles (Q1-Q3).
- The following variables will be compared among study groups:
  - **Severity and demographics.** Age at inclusion, gender, weight, (enrollment) acute pathophysiology and chronic health evaluation (APACHE) II score, (enrollment) Charlson Comorbitdy Index (CCI), baseline SOFA score (identified as the worst SOFA within any 24h between screening and randomization), sepsis start date, infection start date, time (days) from hosital admission to enrollment, ARDS at enrollment, mechanical ventilation at enrollment, septic shock at enrollment, laboratory data (the most abnormal value within the last 24h prior to enrollment), microbiological data (from infection start).
  - **Concomittant treatment,** including all medication, including inotropic, antimicrobial, fluids and blood products received at enrollment. Medication througout 28 days will be assessed for cost-effectiveness analysis.
  - **Adequacy** of antimicrobial treatment will be defined as susceptibility of the identified pathogen (if any) to the empirical treatment given 48h after sepsis start, with optimal dosing and penetration to infection site.

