**Missing values**

Missing values will be treated as such, and the number and percentage of patients or events entering each step of the analysis will be provided. The Little’s test will be used to assess whether missing values are missing completely at random.

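### The over-time tests of HLA-DR and cell populations use complete cases only, so they discard valid samples from patients who die or leave hospital before the last draw

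*Supplement*

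**What the plan says.** The SAP, under Analyses for secondary outcomes, plans two kinds of analysis for cell populations and HLA-DR. The first is a comparison by Student's t-test or Mann-Whitney, chosen by distribution. The second concerns change over time: "Overtime changes will be assessed by the k-related samples non-parametric Friedman test, separately per study arm, and the mixed ANOVA test", the latter "with time and study arm as within-subject and between-subject factors respectively". The SAP does not name the days to be entered.

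The sampling days are in the current protocol (version 2). Under Study visits, days 1 and 5 both have "Sampling of 35 ml of venous blood; 3ml is collected into one PAXgene tube", with further EDTA tubes, and day 10 has "Sampling of 33 ml of venous blood; 9ml is collected into one pyrogen-free tube; and 24ml is collected into EDTA-coated tubes". Under Laboratory analysis the EDTA blood is used "partly for flow cytometry, and partly for whole blood immune functional assay". In Appendix V the row "PBMCs isolation" is marked on the same three days. Study visits also ends daily follow-up at discharge or day 28, whichever comes first.

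On missing data the SAP says "Missing values will be treated as such", asks for the number entering each analysis step, and adds Little's test. Neither document gives a rule for a patient who dies or is discharged before a marker sample is due. The SAP's Populations section says the ITT population enters all secondary outcomes. Analyses for secondary outcomes promises ITT for the clinical ones only.

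**The concern.** A Friedman test or a standard mixed ANOVA uses a patient only if every time point entered is present. With three days entered, someone who dies on day 8 contributes nothing to these tests, although the day-1 and day-5 samples exist. The patients kept are those alive, still in hospital and sampled on day 10. If clarithromycin lowers mortality as the trial supposes, this selection is stronger in placebo than in clarithromycin, and the two trajectories then describe differently selected patients.

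Two lesser points go with this. A Friedman test run separately in each arm gives no estimate of the difference between arms; only the arm-by-time term of the mixed ANOVA does. And although "The Kolmogorov-Smirnov test for normality will be conducted" and the SAP allows for skewed markers in the single comparisons, no transformation is stated for the mixed ANOVA.

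Insight into mechanism is a stated aim in the SAP's opening paragraph, and General principles places flow cytometry in the primary manuscript. Readers will lean on these results.

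**Working it through.** **Plan's own figure.** The protocol's Power calculation uses 28-day mortality of 55% v 30%, type I error 0.10 and power 0.80. A two-sided, continuity-corrected two-proportion formula with these inputs gives 55 per arm, as stated. The documents give no figure for the HLA-DR or cell-population analysis itself.

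**Complete-row requirement.** In made-up data on 20 patients and three days, with 6 day-10 values missing, the Friedman test returned no result. With omission it returned exactly the result for the 14 complete rows. A repeated-measures ANOVA refused the incomplete data as unbalanced.

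**Loss to death.** Constant hazard is an assumption. Deaths by day t = 1 − (1 − m)^(t/28), where m is 28-day mortality.

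| | Placebo, m = 0.55 | Clarithromycin, m = 0.30 |
|---|---|---|
| by day 5 | 1 − 0.45^(5/28) = 13.3% | 1 − 0.70^(5/28) = 6.2% |
| by day 10 | 1 − 0.45^(10/28) = 24.8% | 1 − 0.70^(10/28) = 12.0% |
| of 55, alive at day 10 | about 41 | about 48 |

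If instead one third to three quarters of the 28-day deaths fall by day 10, the loss is 18% to 41% v 10% to 22.5%, a gap of 8 to 19 points. Discharges and missed samples come on top; the documents give no figure for them.

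**Numbers in the subset.** SAP General principles limits flow cytometry to sites near the Athens laboratory. Five of the 13 listed sites are in Athens. If all sites enrol evenly (assumption), that is 110 × 5/13 ÷ 2 ≈ 21 per arm. With one third to three quarters of deaths by day 10, completers are about 17 to 12 in placebo and 19 to 16 in clarithromycin.

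**Selection bias with no drug effect on the marker.** Assume log-odds of death by day 10 of −0.8 per SD of baseline marker (exp 0.8 ≈ 2.2-fold odds per SD lower), with the constant-hazard losses above.
- Completers' baseline mean is shifted by +0.18 SD in placebo and +0.09 SD in clarithromycin, a gap of 0.09 SD.
- If baseline and day-10 values have equal SD and correlation r, a baseline shift s carries over as r·s, so the bias in change is (1 − r) × 0.089: 0.027 SD at r = 0.7, 0.045 at 0.5 and 0.062 at 0.3.
- Halving the log-odds gives 0.096 v 0.047 SD, a baseline gap of about 0.05 SD.

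For scale, the standard error of a difference in means is √(1/12 + 1/16) = 0.38 SD to √(1/17 + 1/19) = 0.33 SD. The baseline gap is about a quarter of that.

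Under a different assumption, that change itself correlates 0.3 to 0.7 with survival, the completers-only gap in change is 0.06 to 0.14 SD at constant hazard. It is 0.08 to 0.19 SD if three quarters of the deaths fall by day 10.

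**The case against.** A reader might infer that the whole HLA-DR and cell-population analysis is confined to survivors to day 10. It is not: the t-test or Mann-Whitney comparisons need no complete row, so a patient who dies on day 8 stays in any day-1 or day-5 comparison. They also offer a rank-based option for skewed markers. The loss is confined to the over-time tests.

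A reader might also infer that the plan will claim a drug effect from significance in one arm and not the other. Nothing in the SAP says so, and the mixed ANOVA contains an arm-by-time test.

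Nor is a different loss in each arm a fact of the design. It depends on the assumed 55% v 30% mortality; with no mortality effect the shares would be similar. Because the SAP does not name the days, entering only days 1 and 5 would cut the loss to about 13% v 6%.

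Finally, General principles calls all secondary outcomes exploratory, the numbers entering each step are to be reported, and the primary endpoint is untouched.

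All of this stands, and it limits the point without removing it. The over-time tests still discard usable samples from a small subset, and reported counts need not separate death from discharge. Little's test does not help either: it changes nothing in the analysis, and loss by death is informative.

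**Conclusion.** The point holds for the Friedman tests and the mixed ANOVA, not for the marker analysis as a whole. With days 1, 5 and 10 entered, and the planned mortality at constant hazard, about 25% v 12% are lost to death before discharges are counted. The resulting bias in change is modest, roughly 0.03 to 0.06 SD under the assumed 2.2-fold odds and a baseline to day-10 correlation of 0.7 to 0.3. It could be larger if change itself tracks survival. Both figures rest on assumptions the documents cannot settle. The firmer cost is lost information where perhaps 21 patients per arm are available. This is a cheap improvement to an exploratory analysis; it does not threaten the trial's main conclusion.

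**What to change.** In Analyses for secondary outcomes, replace the mixed ANOVA as the between-arm over-time test with a linear mixed model on all available samples:
- Name the sampling days. Fit arm, day and arm × day.
- Enter the day-1 value as a covariate, or as a response with the arm means constrained equal at baseline. The second form keeps patients who have only a day-1 sample. Under the first, deaths before day 5 (about 13% v 6% on the same assumption) add no outcome data.
- State the transformation for skewed markers in advance.
- Report the between-arm difference on each day with its 95% CI, and keep the within-arm Friedman results descriptive.
- Tabulate the numbers dead, discharged and sampled per arm and day.
- State that truncation by death remains, since no such model removes it.

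The cost is SAP wording and a little more analysis work. SPSS, which the SAP names, fits the model. By its own account the SAP predates unmasking and database lock. The downside is reliance on values being missing at random given the data in the model, which should be said openly.
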